### Outcome measures

*Primary outcome measures*
1.Pancreatic endocrine function: diabetes or impaired glucose tolerance (pre-diabetes) by OGTT or HbA1c, defined using World Health Organization (WHO) cut-offs
^
23
^
2.Pancreatic exocrine function: faecal elastase and serum lipase

*Secondary outcome measures*
1.Pancreas size and structure: Pancreas size and architecture using ultrasound and CT (subsets from all adult cohorts)2.Pancreatic calcification: Calcification determined by CT scan (subsets from all adult cohorts)3.Insulin production and insulin resistance:a.Mathematical modelling of blood glucose, insulin and C-peptide at three (for children) or seven (for adults) times during a 120-minute OGTT for estimation of indices of first phase, second phase and total insulin release, insulin kinetics and insulin resistance;b.Mathematical modelling of data from analytes from IVGTT measured in blood samples collected at -10, -1, 2, 4, 6, 8, 10 minutes: glucose, insulin, and C-peptide (subset from CICADA
*).*
4.Other hormonal contribution to glucose metabolism and diabetes: Incretins (gastric inhibitory polypeptide (GIP) and glucagon-like peptide-1 (GLP-1)) and glucagon at 0, 30, 60, 90 and 120 minutes during an OGTT (subsets from CICADA and St-ATT). The goal is to assess whether insulin resistance is associated with changes in endocrine signals from the gut. The area under the curve of glucagon (AUC glucagon) will be used to assess a possible presence of hyperglucagonemia, often seen in T2D subjects.5.Proinsulin: Proinsulin in baseline samples before OGTT. The baseline proinsulin levels will be used as indicator of β-cell stress/exhaustion in the fasting state where higher levels of proinsulin will indicate higher levels of β-cell stress.6.Abnormal prior pro-insulin/insulin ratio and diabetes (subset): From the CICADA cohort, measurement of pro-insulin and insulin in fasting samples collected four years previously and comparison with current diabetes by OGTT. Like the fasting proinsulin, the pro-insulin/insulin ratio in fasting samples will be used as a surrogate measure of β-cell stress.

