*Anthropometry*:** Anthropometry will use standard methods
^
27
^ conducted by trained staff. At each site technical error of measurement will be assessed and further training provided so that all staff reach acceptable levels of agreement with the local criterion anthropometrist.
^
28
^ Anthropometric measurements will be weight, height, sitting height, tibia length, circumferences of waist, hip and mid-upper arm, and triceps and subscapular skinfold thicknesses.7.
**
*Body composition:*
** All sites will use bioelectrical impedance (BIA) for body composition assessment. Lusaka will additionally use air displacement plethysmography (BodPod) and can assess its agreement with BIA.

The following assessments will be conducted in only subsets of consenting participants.
8.
**
*Detailed OGTT*
**: The same OGTT protocol will be used as above but, for 80 participants in each of the CICADA and St-ATT cohorts, referred to as the in-depth subset, we will measure additional hormones: glucagon, gastric inhibitory peptide (GIP), glucagon-like peptide-1 (GLP-1) at multiple time points and trypsinogen in baseline samples. The in-depth subsets will be randomly selected from the cohort participants, stratified by whether or not they were recorded as previously malnourished in our databases from earlier follow-ups. In event of refusals, replacements will be from the next in the randomised lists.9.
**
*IVGTT:*
** This test is the gold standard for estimating the early insulin response. It will be done only in the in-depth subset from CICADA. Results will be compared with OGTT in the same participants in order to better understand the OGTT results. For this test a solution of sterile 50% dextrose, in amounts 0.3 g/kg body weight, will be injected into the antecubital vein over 60 seconds starting at time 0 minutes. Blood samples will be taken at -10, -1, 2, 4, 6, 8, 10 minutes for measurement of glucose, insulin, C-peptide and glucagon.10.
**
*CT scans*
**: The CT studies will be performed in 100 participants from each of the adult cohorts by qualified and experienced radiologists in identified health facilities. Participants will be randomly selected, similarly to the in-depth subsets. Scans will be taken without use of contrast agents. The protocol will assess the following:•Pancreatic volume (in cm

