### Statistical analyses and sample size calculations

Analyses related to individual hypotheses are described below. Primary analyses will be conducted for each cohort separately. Pooled analyses using all or some cohorts combined will be conducted based on the individual cohort results, and in order to investigate how age at malnutrition and length of time between malnutrition and outcome assessment influence the associations between malnutrition and pancreas structure and function. Analyses will be guided by the conceptual framework in
Figure 1. Sample sizes for the specific hypotheses indicate that, with the available number of participants in the cohorts, we have sufficient power for the main analyses with all participants. For some expensive or labour- and participant-intensive outcomes, we had to consider cost and feasibility and have calculated power for analyses in subsets.

*Hypothesis 1:*
Prior malnutrition is associated with later abnormal pancreatic structure and endocrine and exocrine function.

Participants with and without prior wasting malnutrition, the SAMPA study primary exposure, will be compared within each cohort for all pancreas structure and function outcomes: diabetes by OGTT or HbA1c, exocrine function as indicated by faecal elastase and serum lipase, and pancreas size and presence of abnormalities detected by ultrasound or CT scan. We will initially fit regression models for each outcome with prior malnutrition as the main exposure, controlling for sex and for age as a continuous variable. We will investigate whether there are interactions between prior malnutrition and sex, which is known to be associated with both prior malnutrition and diabetes. We will then investigate whether the associations between malnutrition and the outcomes differ by the following variables:
•Time since malnutrition•Sitting/standing height ratio as an indicator of early life stunting•HIV status for African cohorts only (SAM Lusaka, NUSTART Lusaka, CICADA)

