*i.e.* glucose, hormones, faecal elastase and serum lipase, the available sample size in the smallest cohort will be sufficient to determine differences of 0.4 times the standard deviation with 90% power. Expected differences in pancreas volume were calculated using volume normalised to kg body weight to account for the participant age and size range.
^
35
^ A total of n=100 per cohort (assuming a standard deviation of 0.3 mL/kg) will provide 90% power to detect differences of 0.2 mL/kg between those with/without prior malnutrition, which is a smaller difference than that expected between people with and without diabetes.
^
35
^
^,^
^
36
^

*Hypothesis 2:*
Prior malnutrition is associated with pancreatic calcification which in turn is associated with diabetes.

To investigate whether prior malnutrition is associated with pancreas calcification, from each adult cohort we will randomly select for CT scans 50 participants who were exposed to malnutrition and 50 controls who were not exposed. The presence of calcification or other pancreas abnormalities on CT will be compared between those with or without prior malnutrition.

In order to increase sample size for this and for the second part of the hypothesis comparing calcification with diabetes, results from CT scans in the subset of participants with these will be compared with the ultrasound results from the same participants to indicate whether abnormalities determined by ultrasound, e.g. pancreas body or duct shape, correspond to calcification by CT scan. We will then compare the proportion of abnormalities based on ultrasound or CT scan among those with and without diabetes.

**
*Sample size*
**: Population prevalence estimates for pancreatic calcification appear unavailable so we have not performed any sample size calculations. Pancreatic calcifications are seen in fibro-calculous pancreatic diabetes
^
7
^ but these studies have been conducted on participants selected for their clinical presentation.

*Hypothesis 3:*
The abnormal glucose regulation seen after malnutrition is associated with relative insulin deficiency with or without insulin resistance.

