A deeper understanding of associations between prior malnutrition and the underlying glucose metabolic pathways will be explored through modelling biochemical measures over the course of the two-hour OGTT. Glucose, insulin and C-peptide data from OGTT will be used to model pancreatic cell functionality according to published methods in order to determine a set of indices quantifying: first phase, second phase, and total insulin secretion,
^
37
^ whole-body and hepatic insulin clearance,
^
38
^ and insulin sensitivity.
^
25
^
^,^
^
39
^ For the child cohorts for whom only three blood samples are available over the two-hour OGTT, we will use methods designed to determine insulin sensitivity from sparsely sampled OGTTs.
^
26
^ The IVGTT data from the CICADA cohort subset can be similarly modelled to estimate insulin sensitivity and insulin secretion. Comparison of the indices estimated from the two tests will provide information as to whether altered intestinal function,
*e.g.* glucose absorption or incretin secretion, influences insulin secretion or sensitivity in participants previously malnourished or not.

**
*Sample size*
**: We will use individual data from all SAMPA adult participants and, for children who have only three sample points during OGTT, we will combine data from groups of participants.
^
26
^ Most previous studies in this area include 10-100 people per group, whereas we will be able to study all SAMPA participants.

*Hypothesis 4:*
An abnormal fasting pro-insulin/insulin ratio is associated with later development of diabetes in adults who had malnutrition and infection.

**
*Analysis*
**: We will use the detailed data and samples available from CICADA to investigate whether the proinsulin/insulin ratio in CICADA samples collected from fasted participants about four years prior to the SAMPA visit is associated with diabetes or prediabetes at the SAMPA visit. This will be a nested case-control study where cases are 60 CICADA participants with current diabetes by OGTT and controls are 60 CICADA participants with normal OGTT. These participants will be selected by stratified random sampling. Logistic regression will be used, controlling for age and sex, to determine if prior proinsulin/insulin ratio is associated with later diabetes.

**
*Sample size*

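### The 90% power for 0.4 SD claimed for hormones does not hold for glucagon, GIP and GLP-1, which are measured in only 80 people in each of two cohorts

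*Protocol article*

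**What the plan says.** The opening of Statistical analyses and sample size calculations says that power is sufficient for the main analyses with all participants. For some expensive or burdensome outcomes it adds that "we had to consider cost and feasibility and have calculated power for analyses in subsets". The same section makes the separate analysis of each cohort primary and lets pooling follow from the cohort results.

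The Hypothesis 1 sample-size paragraph then defines the continuous variables, in an i.e. list, as "glucose, hormones, faecal elastase and serum lipase". It states that the smallest cohort is large enough to detect 0.4 SD in them with 90% power. The word hormones carries no restriction.

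Assessments, item 8 (Detailed OGTT), says that "for 80 participants in each of the CICADA and St-ATT cohorts, referred to as the in-depth subset, we will measure additional hormones". It names these as glucagon, GIP and GLP-1 at several time points, plus baseline trypsinogen. Secondary outcome 4 under Outcome measures likewise confines the incretins and glucagon to subsets of CICADA and St-ATT. Selection is random, "stratified by whether or not they were recorded as previously malnourished in our databases from earlier follow-ups". The ratio of previously malnourished to not is not given.

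**The concern.** The power sentence is built on whole cohorts and worded so that it covers every hormone outcome. The article itself calls glucagon, GIP and GLP-1 hormones, yet they are not measured in whole cohorts, and in four of the six cohorts they are not measured at all. A reader would take secondary outcome 4 to be powered like insulin or faecal elastase.

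What is at stake is how a null result is read. If previously malnourished and control participants show no difference in glucagon or incretin response, the stated 90% power for 0.4 SD invites the conclusion that a moderate difference has been ruled out. With 80 people per cohort that conclusion would not be warranted.

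**Working it through.** **Inputs.** The in-depth subset is 80 per cohort in CICADA and St-ATT (Assessments, item 8). The benchmark is 0.4 SD at 90% power (Hypothesis 1, Sample size). Alpha is not stated; I assume 5%, two-sided. The split is not stated; I assume 40 v 40. That has some support: of the CT subset the article says "Participants will be randomly selected, similarly to the in-depth subsets", and the Hypothesis 2 text sets that subset at 50 exposed v 50 unexposed.

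**Formulas (normal approximation).** For a standardised difference d, power = Φ(d/√(1/n₁ + 1/n₂) − 1.960). The detectable difference is (1.960 + z) × √(1/n₁ + 1/n₂), with z = 0.842 for 80% power and 1.282 for 90%. Results were checked with the noncentral t.

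**The plan's own figures first.**
- 0.4 SD, smallest cohort. Table 1 makes this SAM Lusaka, 180 expected. At 100 v 80: √(1/100 + 1/80) = 0.150; 0.4/0.150 = 2.667; Φ(0.707) = 76%. The stated 90% is not reached there. It is reached in NUSTART Lusaka at 200 v 100: 0.4/0.1225 = 3.266; Φ(1.306) = 90.4%. That discrepancy is a separate matter. Here it matters only that either basis is a whole cohort of 180 to 300 people, not a subset of 80.
- CT volume, 50 v 50, 0.2 with SD 0.3: d = 0.667; 0.667/0.200 = 3.333; Φ(1.373) = 91.5%. This reproduces.
- Proinsulin/insulin ratio, 60 v 60, 0.04 with SD 0.07: d = 0.571; 0.571/0.1826 = 3.130; Φ(1.170) = 87.9%, slightly under the stated 90%.

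So two subset outcomes do have a stated figure. The in-depth subset has none.

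**In-depth subset, one cohort, 40 v 40.** √(2/40) = 0.2236.
- Power for 0.4 SD: 0.4/0.2236 = 1.789; Φ(−0.171) = 43.2%; by t test 42.4%.
- Detectable at 80%: 2.802 × 0.2236 = 0.63 SD.
- Detectable at 90%: 3.242 × 0.2236 = 0.72 SD; by t test 0.73 SD.
- Needed for 0.4 SD: 99 per group for 80% power, 132 per group for 90%.

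**Both cohorts combined, 80 v 80.** √(2/80) = 0.1581.
- Power for 0.4 SD: 0.4/0.1581 = 2.530; Φ(0.570) = 71.6%; by t test 71.0%.
- Detectable at 90%: 3.242 × 0.1581 = 0.51 SD; by t test 0.52 SD.

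**Sensitivity to the split (one cohort, 0.4 SD, t test).** 30 v 50 gives 40%; 20 v 60 gives 33%. Any uneven split lowers power, so 40 v 40 is the favourable case.

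**The case against.** The best defence is contextual. The 0.4 SD figure refers to the smallest cohort, where glucagon and incretins are not measured, so hormones could be read as insulin and C-peptide only; item 8 does call the subset assays additional. These outcomes are also secondary and openly described as subset measures. The stated aim of secondary outcome 4 is an association with insulin resistance, and the Hypothesis 1 text calls the mechanistic work, with incretins as its example, exploratory. A journal article may leave power for such measures to the full protocol.

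Much of this stands, and it limits the point. Four stronger readings are tempting but not supported.

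- **That the article contradicts itself on subset power.** The sentence speaks of some outcomes, and the CT and proinsulin figures satisfy it.
- **That the Hypothesis 3 sentence, "whereas we will be able to study all SAMPA participants", is false.** It follows a description of modelling OGTT glucose, insulin and C-peptide, which all participants provide, and for those it is true. The same text identifies the IVGTT as a CICADA subset.
- **That the IVGTT v OGTT comparison has 42% power.** Assessments, item 9, makes that comparison within the same participants. A two-sample figure does not apply to it; 40 v 40 is relevant only to an IVGTT contrast by prior malnutrition.
- **That a combined CICADA and St-ATT contrast must become the main analysis.** The cohorts differ in infection background and in time since the nutritional assessment (1–2 years in St-ATT against 4 to 16 in CICADA, per Table 1), and time since malnutrition is itself a study question. Combining them also still falls short of 80% for 0.4 SD.

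The defence does not remove the wording itself. The article chose to state a power for hormones, without qualification, in a list that defines the continuous variables. Stratifying the subset by prior malnutrition, and the Hypothesis 3 reference to participants with and without it, show that group comparisons are intended there too.

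**Conclusion.** The point holds as a misstated scope, not as a failed calculation: no figure for the in-depth subset exists to reproduce. The stated 90% power for 0.4 SD does not extend to glucagon, GIP and GLP-1. For a malnutrition contrast in one cohort the power for 0.4 SD is about 42%, and the difference detectable at 90% is 0.73 SD, about 1.8 times the stated one (0.73/0.4).

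This rests on two-sided 5%, an even split and an unadjusted two-group comparison. The 0.4 SD benchmark is the article's own but was set for whole cohorts; the article names no target difference for these hormones. Because the outcomes are secondary and the mechanistic work is called exploratory, this should be corrected but does not threaten the main analyses.

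**What to change.** 1. In the Hypothesis 1 sample-size paragraph, limit the hormones clause to those measured in all participants: insulin and C-peptide.
2. State the in-depth subset's split and its own detectable differences. At 40 v 40 and two-sided 5% these are 0.63 SD at 80% and 0.73 SD at 90% power in one cohort, and 0.52 SD at 90% for both cohorts combined.
3. Describe the subset's contrasts by prior malnutrition as exploratory, to be reported with confidence intervals, so that a null result is not read as absence of a moderate difference.
4. Optionally, prespecify a cohort-adjusted combined CICADA and St-ATT estimate, with heterogeneity reported, alongside the per-cohort results. Fixing it in advance stops it from depending on what those results show. It need not replace them as the main analysis.
5. At most, add a note to the Hypothesis 3 sample-size text that the IVGTT and incretin measures come from subsets only.

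The cost is a few sentences, a less favourable stated figure and, if item 4 is adopted, one further model. No participants or assays are added.

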**3.**	** *CICADA (Chronic Infections, Co-morbidities and Diabetes in Africa), Mwanza, Tanzania* ** The CICADA cohort, ^ 17 ^ total n=1947, comprises three subgroups: a) Tuberculosis patients and controls from the TB-NUT study whose HIV and nutritional status ~16 years ago at recruitment are known (50% BMI<18.5 kg/m ^2^) as well as more recently recruited HIV-infected and uninfected people (controls) ^ 18 ^ ^,^ ^ 19 ^ b) NUSTART, conducted 2010-2014, was a two-site (Mwanza and Lusaka) trial of food supplements for malnourished (BMI<18.5 kg/m ^2^) HIV-infected adults, recruited when starting antiretroviral therapy. ^ 20 ^ In Mwanza, 704 participants were recruited, 409 were alive and followed at the 12-week NUSTART end-point; 273 were available at a follow-up two-three years after starting ART and 206 were recruited to the CICADA study. c) HIV-infected and uninfected people, both malnourished and well-nourished, recruited 3-four years ago for HIV, nutrition and diabetes assessments *CICADA has the most detailed longitudinal diabetes data of the project cohorts, archived fasting samples, and are the oldest so have had longer to develop diabetes; therefore, this cohort will be used for the in-depth and longitudinal components.*	CICADA (TB-NUT) 16 y prior: 450 total • 73 (16.2%) BMI <17 kg/m ^2^ • 74 (16.4%) BMI 17 to 18.5 kg/m ^2^ • 303 (67.4%) BMI > 18.5 kg/m ^2^ CICADA (NUSTART) 11 y prior: 208 total • 105 (50.5%) BMI <17 kg/m ^2^ • 103 (49.5 %) BMI 17 to 18.5 kg/m ^2^ CICADA (New HIV +/- cohort) 4 y prior: 1293 total • 109 (8.4%) BMI <17 kg/m ^2^ • 171 (13.3 %) BMI 17 to 18.5 kg/m ^2^ • 1009 (78.3%) BMI >18.5 kg/m ^2^ Expected for SAMPA: 1412 total
**4.**	** *NUSTART, Lusaka, Zambia* ** 200 previously malnourished HIV-infected adults will be traced and recruited from the NUSTART Lusaka participants. ^ 20 ^ We will also recruit 50 HIV-infected and 50 non-HIV-infected, not previously malnourished, neighbourhood controls.	• 10 y prior: 1111 total, 437 (39%) BMI 17 to 18.5 kg/m ^2^, 674 (61%) BMI<17 kg/m ^2^ • Expected for SAMPA: 300 total

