### Pre-processing of data and descriptive analyses

Fat and fat-free mass in kg will be divided by height in meters-squared, analogous to determining BMI from weight and height, to give fat mass index (FMI) and fat-free mass index (FFMI).

Socioeconomic status (SES) indices will be derived separately for each site using principal component analysis (PCA) of individual or family assets; the specific assets will differ by site since they have been chosen to be locally appropriate. The first component from the PCA will be divided into terciles for use in analyses.

Site-specific diet patterns will be calculated by PCA of food groups; the number of components to include will be based on eigenvalues and scree plots.
^
29
^ The level of adherence to individual patterns will be calculated by dividing the components in terciles.

Descriptive analysis will be conducted within cohorts and divided by sex. Means and standard deviations (SDs) will be used to summarise normally distributed data and medians and interquartile ranges (IQR) for non-normally distributed variables. Categorical variables will be described as proportions.

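### In NUSTART Lusaka every exposed person but only half the controls have HIV, and the stated model omits HIV, so the malnutrition estimate carries about half of any HIV effect

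*Protocol article*

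**What the plan says.** Protocol article, Study cohorts, Table 1, NUSTART Lusaka row. The exposed group is fixed as follows: "200 previously malnourished HIV-infected adults will be traced and recruited from the NUSTART Lusaka participants". For the unexposed: "We will also recruit 50 HIV-infected and 50 non-HIV-infected, not previously malnourished, neighbourhood controls". The row total is "Expected for SAMPA: 300 total". The CICADA row describes the parent trial as enrolling "HIV-infected adults, recruited when starting antiretroviral therapy", so HIV infection was an entry condition for the exposed group.

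Protocol article, Statistical analyses and sample size calculations. The unit of analysis is stated: "Primary analyses will be conducted for each cohort separately". Under Hypothesis 1 the initial models are fitted "with prior malnutrition as the main exposure, controlling for sex and for age as a continuous variable". A sex interaction is examined next. Then comes a list of variables by which the association might differ, which includes "HIV status for African cohorts only (SAM Lusaka, NUSTART Lusaka, CICADA". Later steps deal with BMI, fat and fat-free mass indices and diet patterns. No step adjusts for HIV as a confounder in NUSTART Lusaka or restricts the comparison there to HIV-infected people.

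The Introduction says that infections able to affect the pancreas will be taken into account. The Figure 1 legend lists HIV status among possible modifiers.

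**The concern.** HIV status is unbalanced by design between the two groups that the model compares. If HIV infection or its treatment affects glucose, elastase, lipase or pancreas size, a sex-and-age model attributes part of that effect to malnutrition. The distortion could create an association or hide one.

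The single role that the protocol gives HIV in this cohort, effect modification, does not repair this, because the data needed for it will not exist. The cohort's malnutrition estimate for the main exposure would then not be interpretable as an effect of malnutrition. It would also feed into any pooled analysis.

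**Working it through.** **Inputs.** Table 1: exposed 200, all with HIV; controls 100, of whom 50 have HIV. Sample size text under Hypothesis 1: 0.4 SD with 90% power for continuous outcomes in the smallest cohort; 7% prevalence of 2-hour glucose ≥7.8 mmol/L without malnutrition; differences of 3% to 9% in earlier studies. Assumed: two-sided alpha 0.05 (not stated), SD = 1 within each HIV group, normal approximation, no allowance for sex and age. The HIV effect d is not in the documents, so a range is used.

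**The plan's own power figure.** Power = Φ(0.4/SE − 1.96), with SE = √(1/n₁ + 1/n₀).
- NUSTART Lusaka, 200 v 100: SE = √(0.005 + 0.010) = 0.1225; 0.4/0.1225 = 3.27; power 90.4%.
- SAM Lusaka, the smallest cohort in Table 1 (180 expected): 76.5% at 90 v 90, or 77.4% at the earlier 100 v 85.

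So 90% is not reproduced for the literally smallest cohort. It does agree with NUSTART Lusaka if all 100 controls are counted, including those without HIV.

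**Imbalance and bias.** HIV is 200/200 = 100% in the exposed and 50/100 = 50% in controls. With no HIV term, bias in the mean difference = (1.0 − 0.5) × d = 0.5d.

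**False-positive rate with no malnutrition effect.** The control group mixes two HIV strata, so SE = √((1 + 0.25d²)/100 + 1/200). The rate is Φ(0.5d/SE − 1.96) + Φ(−0.5d/SE − 1.96).

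| Assumed HIV effect d (SD) | Spurious difference (SD) | False-positive rate |
|---|---|---|
| 0.1 | 0.05 | 7% |
| 0.2 | 0.10 | 13% |
| 0.3 | 0.15 | 23% |

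For the binary outcome, suppose that HIV adds 3 to 9 percentage points to 7%. The spurious difference is then 1.5 to 4.5 points, which overlaps the lower part of the 3% to 9% range.

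**Is the HIV interaction estimable here?** Let M = malnourished and H = HIV-infected. Everyone with M = 1 has H = 1, so M×H = M for all 300 people. The design matrix (intercept, M, H, M×H) has rank 3, not 4. The interaction cannot be estimated.

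**The HIV-comparable contrast.** With H as a main effect, the variance of the M coefficient is 1/200 + 1/50 = 0.025, the same as restricting to HIV-infected people (200 v 50). SE = 0.1581.
- Power at 0.4 SD: Φ(0.4/0.1581 − 1.96) = Φ(0.57) = 71.6%.
- Difference detectable with 90% power: (1.960 + 1.282) × 0.1581 = 0.51 SD, against 3.242 × 0.1225 = 0.40 SD with all 100 controls.

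**The case against.** The sex-and-age model is described as the initial one. The Introduction promises to take infections into account, and HIV is then named for this very cohort. An analyst examining HIV would normally include its main effect. Once the empty cell removes the product term, what is left is the HIV-adjusted contrast, and stratifying by HIV gives 200 v 50 directly. On this view a condensed article has only left the final covariate set to the analysis plan.

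Part of this stands: HIV is not overlooked, and the protocol's own step comes close to the right comparison. But the text gives HIV a definite role that cannot work here, and nothing says that the HIV-adjusted coefficient becomes the malnutrition estimate. That is a rule fixed badly rather than a detail left out.

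The objection is also right that every HIV effect used above is assumed, and that 0.5d ignores sex and age adjustment.

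Some wider readings are tempting but not supported:
- **CICADA has the same structure.** Prior BMI below 18.5 does differ across its sources (147/450 = 33%, 208/208 = 100%, 280/1289 = 22%). However, its newest subgroup includes people with and without HIV at both nutritional levels, so the HIV interaction can be estimated there. HIV by exposure is not tabulated, so the amount of confounding cannot be derived. Adding source study would not be free either: the 208 people from the fully exposed source, 33% of the 635 exposed, would drop out of the contrast, and source tracks time since malnutrition.
- **Socioeconomic status must be in the base model.** The protocol says "The first component from the PCA will be divided into terciles for use in analyses" without naming the model. Which model it enters is ordinary analysis-plan detail, as is adjustment for birth weight in CLHNS.
- **NUSTART Lusaka is the cohort meant to isolate malnutrition.** The protocol gives it no such role.

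**Conclusion.** The point holds for NUSTART Lusaka, one of six cohorts. Followed as written, its malnutrition coefficient contains about half of any HIV effect, and the planned HIV step cannot separate the two. That rests only on the group sizes in Table 1 and the stated model. The false-positive rates are illustrations over an assumed range, and the real bias could run in either direction. If HIV has no effect on an outcome, there is no bias for that outcome.

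This should be corrected before analysis, because it concerns the main exposure and the remedy needs no new data. The power available for the interpretable contrast is about 72% at 0.4 SD.

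**What to change.** For NUSTART Lusaka, in the Hypothesis 1 analysis text:
1. Name as the primary malnutrition estimate the model with HIV status as a main effect added to sex and age, or equivalently the comparison among HIV-infected people only (200 v 50).
2. Report the 50 HIV-uninfected controls as a separate reference group.
3. Remove NUSTART Lusaka from the cohorts listed for the malnutrition-by-HIV analysis.
4. State power for this contrast: about 72% at 0.4 SD, or 0.51 SD detectable with 90% power.

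HIV status is known by design, so this changes wording only. The cost is precision: the effective control group falls from 100 to 50. Keeping 90% power at 0.4 SD with 200 exposed would take 1/((0.4/3.242)² − 1/200) ≈ 98 HIV-infected controls. That would be a recruitment decision, and the correction does not depend on it.
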